### Recruitment

Since 87% of Dutch women receive midwife-led care at the onset of pregnancy, participants will mainly be recruited via midwifery practices (n ≈ 60) throughout the Netherlands. Midwives will inform eligible patients about the study (e.g., provide flyers) and ask women to be approached by a researcher through e-mail. Women are also recruited via short study leaflets and posters/flyers disseminated in waiting rooms, via advertising using social media, at pregnancy and baby shows/exhibitions, and directly via the study trial’s website. Women themselves or their midwives will submit the client’s contact-details on a secured access page of the study website. Subsequently, women will receive a complete subject information sheet and informed consent form via regular mail and e-mail with a charge-free return envelope. Women will be offered at least one week to consider their participation. If no response is received after two weeks, women will be sent an e-mail to remind them of the research and informed consent form.

### Study procedure

After providing and receiving informed consent, all participants will be screened for depressive symptoms through online completion of a digital version of the EPDS and, if the score is ≥ 11, followed by a 10–15 minutes telephone interview (MINI) to assess the severity of the depressive symptoms and to assess whether the participant meets DSM-5 criteria for current depressive or dysthymic disorders and suicidality. Master’s students in clinical or research psychology will conduct interviews. A healthcare psychologist with expertise in treating women in the antepartum and postpartum period will train the students.

In line with international guidelines for psychosocial care (NICE-Guideline, 2014) and from a medical-ethical perspective, all participants will receive feedback about their EPDS symptom level and, if applicable, about the psychiatric telephone-interview outcome. A copy of the two-step screening procedure results will also be shared with the participants’ midwife or obstetrician (for which participants gave informed consent). Midwives or obstetricians will be advised to discuss the outcome with their client and further monitor their client’s symptoms if screening results indicate a subclinical depression. If the MINI psychiatric interview identifies (suspected) major depressive or dysthymic disorder or suicidal ideations, they will be advised to refer women to specialized mental healthcare.

To randomly allocate pregnant women with subclinical depression to the intervention or control condition for the RCT, an independent statistician from the department of Epidemiology and Biostatistics (VUmc) will provide a computer-generated blocked randomization sequence in a 1:1 ratio, stored in individual sealed opaque envelopes. Block sizes will be undisclosed to ensure concealment. Following each RCT inclusion, a research assistant will open the next envelop and allocate the participant to the intervention or control condition. After randomization, participants in the control condition will be informed by mail that they will receive care as usual from their midwife or obstetrician. Participants randomized to the intervention condition will receive the ACT-based self-help book and its pregnancy adapted supplement.

After the screening procedure (T0), all study-participants will receive URL-links to the digital baseline- (T1) and follow-up questionnaires (T2-T4; Fig. 1). Each digital questionnaire assessment (T1-T4) will take approximately 30 minutes to complete. Researchers can analyze data collected through this web-based data-gathering tool without having access to information about the allocation.

For the HCC sub-study, a subsample of women will be asked to donate a hair sample at T1 (100 women with EPDS score < 11; 150 women with subclinical depression; 50 women with major depressive or dysthymic disorder based on the MINI). Hair samples will be collected at 14 to 20 weeks’ gestation. Due to COVID-19, partners (or other family members) will be asked to collect the participants’ hair samples at home. An instruction video will be shared for this purpose. Participants and their partners will be instructed to watch this video before hair sample collection to ensure a standardized hair sampling method. Hair strands of approximately 100 to 150 hairs will be cut as close as possible from the scalp from a posterior vertex position [42]. The most proximal 3 cm of hair will be used for laboratory analysis. Based on a mean hair growth rate of 1 cm per month, the hair samples reflect the cumulative cortisol and cortisone secretion of the previous 3 months. Participants of the HCC sub-study will be asked to provide additional written informed consent.

For the qualitative sub-study, a sub-sample of women from the intervention arm will be recruited via ‘purposively sampling’ approximately two weeks after the post-intervention assessment (T2). They will participate in a qualitative interview of 30–40 minutes (provided they have given additional consent). Interviews will be conducted using a topic-list with open-ended questions addressing the following substantive points during the interviews: (emotional) experience of the resilience-course, experiences of the e-mail coaching, working mechanisms, and point(s) of improvement of the intervention. Counselors will also be interviewed concerning the course of the intervention. A trained interviewer will conduct interviews. Results will provide important information for (process)evaluation, optimization, and future implementation of pregnant subclinically depressed women’s resilience course.

### Intervention

Participants in the intervention group will receive the ACT-based self-help book with 9 weekly modules [43]. They will also receive a pregnancy-specific supplement written by one of the developers of the ACT-based self-help book (author [name]) and two psychologists with expertise in perinatal psychology (authors [name] and JH). The supplement includes psychoeducation about depressive symptoms during pregnancy and explanations of ACT. The self-help book approach consists of acceptance, commitment, and mindfulness-based strategies and behavioral change strategies to increase psychological flexibility and resilience through six main ACT processes: acceptance, cognitive diffusion, being present, self as context, values, and committed action [44]. Each week, participants will follow one of the nine modules of the self-help book ‘Living to the Full’ [43]. The participants will reflect on their avoidance and control strategies and learn how to stop them and come into contact with their recent experiences. The book also focuses on raising awareness of significant personal values and subsequent decision making based on these values [45]. Each module takes about 2–3 hours a week (e.g., reading, homework, practicing). Daily mindfulness exercises of 10 to 15 minutes to reduce stress are encouraged and provided on audio. After each week, participants will receive motivational support through e-mails from trained counselors from the department of Clinical Psychology. Counselors will send an e-mail with questions about the progress during the previous week (e.g., ‘Were you able to perform the exercises in this module?‘). Participants are instructed to respond within two days, after which they receive a feedback e-mail from the counselor. The purpose of e-mail support (of approximately 10 minutes a week in total) is supporting participants in performing their homework and exercises and providing answers to questions about the self-help booklet [45]. The intervention condition and online counselors will be supervised by a clinical psychologist to monitor women’s possible worsening of symptoms. For the latter, symptom improvement or deterioration will be assessed every two weeks in both the intervention and control group with the Patient Global Impression of Change scale (PGI-C) [46].

### Care as usual

CAU comprises regular antepartum appointments with maternity healthcare professionals. Because of the RCT’s practice-oriented nature and ethical reasons, midwives can refer women of both the intervention and CAU groups for further psychological/psychiatric treatment if indicated and desired by the woman. All mental healthcare received by women from both RCT groups will be assessed at T2 (post-treatment). As a consequence of this study’s design, neither participants nor researchers can be blinded to group allocation. However, to avoid potential contamination, the study information letter initially provided to potential participants will not include details regarding the type of intervention (e.g., ACT [43]).

### Trial status

The cohort study with embedded RCT started enrolling on April 20, 2019. Currently, 757 participants have been enrolled in the cohort of whom 60 participate in the RCT.

## Assessments

### Primary outcomes

Depressive symptoms will be assessed with the 10-item Edinburgh Postnatal Depression Scale (EPDS) [47, 48]. The EPDS has been validated to screen for mild or major depression both antepartum and postpartum [49]. A Dutch validated EPDS version with good internal validity with a Cronbach’s alpha of 0.83 [48] and good concurrent and predictive validity is available [38]. The ten items’ response options range from 0 to 3, with higher scores indicating more depressive symptoms. For inclusion, a cut-off of ≥ 11 will be used since sensitivity and specificity for depression at this cut-off are estimated to be 0.83/0.90 in the antepartum period [18, 38, 50].

Resilience will be measured with the Dutch version of the Mental Health Continuum-Short Form (MHC-SF) (T2-T4; Table 1). Mental health or well-being acts as a resilience resource that buffers against psychopathology. The MHC-SF has 14 items that are scored on a 6-point scale ranging from 0 to 5 (never, rarely, sometimes, regularly, often, or (almost) always) and captures three dimensions: emotional (3 items), psychological (6 items) and social well-being (5 items) over the past 4 weeks. The Dutch version has shown good psychometric properties, is reliable (internal reliability of alpha 0.89 on MHC-SF total; and alpha’s of resp. 0.83, 0.83, and 0.74 on emotional, psychological, and social well-being subscales resp.) and was validated in a Dutch sample (n = 1621) [51]. With the MHC-SF, well-being can be distinguished into flourishing, neither flourishing nor languishing, and languishing (i.e., absence of well-being) [52].

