**Methods:**

Pregnant women (≥ 18 years) receiving care in Dutch midwifery practices will participate in a prospective cohort study (n ~ 3500). Between 12 and 18 weeks of pregnancy, all women will be screened for depression with the Edinburgh Postnatal Depression Scale (EPDS). Women with an EPDS score ≥ 11 will be evaluated with a structured clinical interview. Participants with subclinical depression (*n* = 290) will be randomized to a 9-week guided self-help ACT-training or to care as usual (CAU). Primary outcomes (depressive symptoms and resilience) and secondary outcomes (e.g. anxiety and PTSD, bonding, infant development) will be collected via online questionnaires at four prospective assessments around 20 weeks and 30 weeks gestation and at 6 weeks and 4 months postpartum. Maternal hair cortisol concentrations will be assessed in a subsample of women with a range of depressive symptoms (*n* = 300). The intervention’s feasibility will be assessed through qualitative interviews in a subsample of participants (*n* = 20).

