## Method

### Study design

This study is designed as a prospective cohort study with an embedded randomized controlled trial (RCT) (Fig. 1). All women participating in the cohort study will be screened for depression at 12–18 weeks gestation. Women with subclinical depression will then be randomly allocated to either a guided self-help resilience program of 9 weeks (intervention) or care as usual (CAU) provided by maternity healthcare providers. All participants will be assessed at approximately 14–20 weeks (T1, RCT pre-intervention), at 28–32 weeks (T2, RCT one week post-intervention) gestation and postpartum at 6 weeks (T3) and 4 months (T4). Birth outcomes at T3 will be derived through data-linkage with the Dutch national perinatal registry [37]. Two additional sub-studies will be conducted to assess: (1) maternal cortisol levels (hair cortisol concentration (HCC)) in 300 participants randomly selected from the cohort study following T0, and (2) feasibility of the intervention via interviews with approximately 20 participants in the intervention group following T2. The Ethics Review Board of the VU University Medical Center has approved the study protocol (certificate number NL64740.029.18).

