### Statistical analyses

Analyses for the RCT will be done on both intention to treat (ITT) and per-protocol basis. First, to assess differences in depressive symptoms (EPDS) and resilience (i.e., well-being assessed with the MHC-SF) between intervention and control condition, independent t-tests will be used. The mean change of scores (T2-T1) will be standardized to interpret effect sizes in terms of Cohen’s d [83]. Next, ITT analyses will be performed using linear mixed modeling (LMM) to adequately deal with repeated measures data and clustering (i.e., at midwifery practice level). LMM’s with time, treatment, and time-by-treatment interactions will be performed to assess the intervention’s effectiveness in improving continuous primary outcomes of depressive symptomatology, resilience, and continuous secondary outcomes such as infant developmental milestones. Chi-square tests will be performed to assess group differences according to dichotomous (secondary) outcomes such as subclinical depression and flourishing incidence. Subsequently, generalized (binary) linear mixed models (GLMM) will be used to assess the intervention’s effect on the dichotomous secondary outcomes. To identify predictors of successful resilience training, (generalized) linear mixed models will be used. A multivariable GLMM to identify potential predictors of treatment success will be conducted in two steps: (1) univariable analyses to examine whether the potential predictor is significantly associated with the dichotomous outcome and (2) including significant predicting variables (*p* < .10) in the final multivariable model to identify independent predictors using the forward selection procedure. Finally, moderation and mediation analyses will be conducted to explore possible working mechanisms (psychological flexibility and mindfulness) of the intervention on maternal depressive symptomatology, resilience, and behavioral and infant developmental outcomes.

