For the longitudinal data, latent class analyses will be used to explore different trajectories of depressive symptoms based on four repeated assessments over time. Correlates (e.g., cortisol levels) of perinatal depressive trajectories over time will be identified by using (generalized) linear mixed models. Associations between prenatal resilience and maternal mental health outcomes, birth, and infant developmental outcomes will be examined by using linear mixed models and GEE-analyses. All (main) analyses will be adjusted for potential confounders such as parity, educational level, and ethnicity. Multiple imputation methods will be used to impute missing values if missing at random can be assumed.

Audio-recorded qualitative interviews will be transcribed and anonymized. Transcripts of the interviews will be coded in an open, axial, and selective manner. Thematic analysis will be performed by two researchers [84]. After coding the first 3 or 4 interviews separately, both researchers will discuss the findings to modify the coding process. The software program MAXQDA will be used to facilitate the analysis process.

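### The stated T2–T4 schedule for the second primary outcome (MHC-SF) contradicts the planned T2–T1 change and the abstract's four assessments

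*Protocol article*

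**What the plan says.** The protocol article names two primary outcomes, depressive symptoms (EPDS) and resilience (MHC-SF). Four places bear on when the second is measured and how it is analysed.

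- **Assessments, Primary outcomes:** "Resilience will be measured with the Dutch version of the Mental Health Continuum-Short Form (MHC-SF) (T2-T4; Table 1".
- **Study design:** "All participants will be assessed at approximately 14–20 weeks (T1, RCT pre-intervention), at 28–32 weeks (T2, RCT one week post-intervention". T1 is therefore before the intervention, and T2 is the first assessment after it. T3 and T4 are postpartum.
- **Statistical analyses:** "to assess differences in depressive symptoms (EPDS) and resilience (i.e., well-being assessed with the MHC-SF) between intervention and control condition, independent t-tests will be used", followed directly by "The mean change of scores (T2-T1) will be standardized to interpret effect sizes" as Cohen's d. The effectiveness analysis is then a linear mixed model with time, treatment and their interaction, for both primary outcomes.
- **Abstract, Methods:** "Primary outcomes (depressive symptoms and resilience) and secondary outcomes" (the latter with examples) "will be collected via online questionnaires at four prospective assessments around 20 weeks and 30 weeks gestation and at 6 weeks and 4 months postpartum".

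The Primary outcomes section refers to Table 1 for the schedule. The content of Table 1 is not reproduced in the text at hand.

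**The concern.** A change from T1 to T2 needs a score at T1. Taken literally, the Primary outcomes section gives the MHC-SF no score there, yet the analysis section treats it in the same way as the EPDS. Two things are at stake if the literal schedule is the one in use.

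1. The stated effect measure for one of the two primary outcomes would have no data.
2. The mixed model for that outcome would contain only post-intervention times. Its interaction would then ask whether the arms drift apart or together after the training has ended, and not whether the training worked.

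The matter is also time-critical. A pre-intervention score that was not collected cannot be recovered later.

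**Working it through.** **Step 1. Set the statements side by side.**

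| Place | MHC-SF at T1? |
|---|---|
| Primary outcomes | No (T2–T4) |
| Statistical analyses | Required (T2–T1 change) |
| Abstract, Methods | Yes (four assessments, the first around 20 weeks) |
| Table 1 | Not visible |

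The first row is incompatible with the second and the third. Whatever Table 1 holds, at least one passage of running text needs correcting.

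**Step 2. What the interaction estimates under each schedule.** Let δ be the between-arm difference at T2, and suppose that it is sustained at T3 and T4. Randomization makes the expected difference at T1 zero.

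- With T1–T4 and T1 as reference: the interaction at T2 is δ − 0 = δ, and likewise at T3 and T4. The interaction carries the effect.
- With T2–T4 and T2 as reference: the interactions at T3 and T4 are both δ − δ = 0. The effect sits wholly in the treatment term, which equals δ.

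So on the literal schedule the interaction is expected to be null for an effect that is fully present at T2 and then held. The treatment term at T2 still shows it.

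**Step 3. Is the sample size affected?** Inputs from the Power calculation section: α = 0.05 (sidedness not stated; two-sided assumed), power 80%, d = 0.33, attrition 18%. Allocation is 1:1 (Study procedure).

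- n per arm = 2(1.960 + 0.842)² / 0.33² = 15.70 / 0.1089 ≈ 144.2, rounded up to 145, so 290 in total. The stated figure is 290.
- Retained: 290 × 0.82 = 237.8, or 118.9 per arm. The detectable d from the noncentral t distribution is 0.365. The stated figure is 0.365.

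Both figures reproduce with a plain two-group comparison. Neither uses a T1 MHC-SF score, so neither depends on how the contradiction is resolved.

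**Step 4. Illustration only: what a T1 score does to precision.** The article gives no T1–T2 correlation ρ for the MHC-SF, so a range of 0.3 to 0.7 is assumed. Detectable differences are in raw-score SD units with about 238 women analysed.

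| Analysis | Formula | ρ = 0.3 | ρ = 0.7 |
|---|---|---|---|
| T2 only | 0.365 | 0.365 | 0.365 |
| T2–T1 change | 0.365 × √(2(1 − ρ)) | 0.432 | 0.283 |
| Baseline-adjusted T2 | 0.365 × √(1 − ρ²) | 0.348 | 0.261 |

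The change score is less precise than T2 alone when ρ is below 0.5. The adjusted analysis is not in the plan. The table therefore does not measure a loss that the contradiction causes.

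**Step 5. How much can still be changed.** The Trial status section reports 60 women in the RCT. 290 − 60 = 230 were still to be randomized, and 230 / 290 = 79%.

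**The case against.** The strongest reply is that this may be a one-character slip. The schedule is delegated to Table 1, which cannot be seen, and a planned T2–T1 change makes little sense unless the authors meant to collect T1. That stands. A reader might infer that the trial has no baseline for resilience, but the article does not show this. The abstract is also weak evidence for T1, since the same sentence places secondary outcomes such as infant development at the four assessments, two of which precede birth. The weight therefore rests on the conflict between the Primary outcomes and Statistical analyses sections.

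Three further inferences are tempting and should not be drawn.

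- **That a planned baseline adjustment is lost.** None is planned. The model terms are time, treatment and their interaction, and the adjusters named as examples are parity, educational level and ethnicity.
- **That the MHC-SF cannot be analysed at all.** A t-test between arms at T2 could be run, and so could the T2 treatment contrast within the mixed model. The EPDS analyses are not touched.
- **That the cohort work is seriously compromised.** The plan says "Associations between prenatal resilience and maternal mental health outcomes, birth, and infant developmental outcomes will be examined" without naming the instrument in that sentence. If it is the MHC-SF, T2 is still before birth, and the women already trained by then would be at most about 145 of roughly 3500 (4%).

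What the reply does not remove is the contradiction. The article itself states both the time points and the change score, so this is not a detail left to a fuller document.

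**Conclusion.** The point holds as an internal contradiction about when a primary outcome is measured. It does not hold as proof that the baseline is missing.

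Its consequences are conditional. If the T2–T4 schedule is a slip, the error is confined to the text. If it is literal, the MHC-SF change score and its Cohen's d cannot be computed, and the interaction alone would not detect a benefit present at T2 and sustained. That second result assumes a constant between-arm difference from T2 to T4. In either case the sample size of 290 and the detectable d of 0.365 stand.

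It needs resolving because it concerns the stated effect measure of one of two primary outcomes, and because most of the RCT sample was still to be enrolled when the article appeared.

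**What to change.** Reconcile the Primary outcomes section with the abstract, the Statistical analyses section and Table 1, and state plainly whether the MHC-SF is collected at T1.

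- **If it is collected at T1:** change T2–T4 to T1–T4 in the text. The cost is a one-line correction.
- **If it is not:** add the MHC-SF to the online T1 questionnaire for women still to be enrolled. Define its effect as the between-arm contrast at T2, estimated in a longitudinal model that tolerates a missing baseline. Do not define it as the T2–T1 change or through the interaction alone. One suitable form treats T1 as an outcome occasion with a common mean in both arms, so that women already enrolled without a T1 score still contribute.

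The second route costs 14 items in a questionnaire of about 30 minutes, plus a small amendment. Neither route changes the sample size.
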